### 4.3. Implementation of This Intervention

Implementation of the intervention program is likely to impact its success; therefore, several strategies will be used to facilitate correct implementation of the intergenerational movement program by different organizations (e.g., Family Sports Flanders and Sports Flanders). First, a detailed protocol will be written to assure that the intervention will stay theory-based and to minimize attrition rates, which will both foster the success of the intervention (i.e., this protocol will be the common thread; researchers, stakeholders, grandchildren, and grandparents should respect this protocol). Second, the expert meetings with diverse stakeholders from different organizations (e.g., GRAY, Family Sports Flanders, and MOEV) that will be held after the co-creation trajectories will help to gain feedback and additional advice about the feasibility of implementing the cognitively enriched movement activities for grandchildren and grandparents (e.g., body posture, execution of movements, and other aspects that require attention). This input will also be integrated into the protocol. Third, the planned pilot study will help to refine the cognitively enriched movement activities to ensure that they will be useful and correctly executed, as well as attractive and feasible for the target population. If results of the RCT show that the intervention is indeed effective at improving co-PA and cognitive functioning in the first place, and psychosocial well-being and the quality of the family relationship in the second place, a meeting with organizations who are interested in implementing this intergenerational movement program will be held to discuss the information necessary for grandparents, parents, and children, which materials are needed, which locations are preferable and feasible, which certified teachers should be recruited, etc. A very important factor is that the embedding of this project in GRAY will help to engage Flemish partners, such as Family Sports Flanders and Sports Flanders, in its execution, dissemination, and valorization.

## 5. Conclusions

This will be the first intergenerational movement program targeting grandchildren and grandparents using the BCW in combination with a co-creation approach and using a combination of PA and cognitively enriched PA. Developing and evaluating this intergenerational, cognitively enriched movement program might be effective in improving co-PA, cognitive functioning, psychosocial well-being, and the quality of the family relationship in both grandchildren and their grandparents. If the program seems to be effective, it could be implemented in different organizations in Flanders, and it could have important implications for future research and health policies. Targeting grandchildren and their grandparents for participation in an intergenerational cognitively enriched movement program might be a novel and effective approach to improving general health in both age groups.

## Figures and Tables

**Figure 1 ijerph-19-07150-f001:**
[figure not shown]
Overview and timeline of the GRANDPACT Project.

**Figure 2 ijerph-19-07150-f002:**
[figure not shown]
The eight steps of the Behaviour Change Wheel used in the GRANDPACT co-creation trajectories.

**Figure 3 ijerph-19-07150-f003:**
[figure not shown]
The three sources of behaviour and the TDF Domains of the Behaviour Change Wheel. “Adapted with permission from [47]. 2017, Lou Atkins”.

**Figure 4 ijerph-19-07150-f004:**
[figure not shown]
Overview of the study design and number of participants [58,59,60].

**Figure 5 ijerph-19-07150-f005:**
[figure not shown]
Overview of the RCT with the pre- (baseline), post- (after 24 weeks) and follow-up (after 36 weeks) measurements.

## Data Availability

Not applicable.

## Appendix A

**Table A1 ijerph-19-07150-t0A1:** TIDieR (Template for Intervention Description and Replication) Checklist. (Information to include when describing an intervention and the location of the information).

Item Number	Item	Where Located **	
		Primary Paper (Page or Appendix Number)	Other ^†^ (Details)
	**BRIEF NAME**		
1.	Developing and evaluating an intergenerational movement program for grandchildren and their grandparents using the Behaviour Change Wheel in combination with a co-creation approach. The effects of this intergenerational movement program on co-PA, physical activity, cognitive functioning, psychosocial well-being, and quality of the family relationship in grandchildren and their grandparents will be measured.	p. 1	______________
	**WHY**		
2.	It is decided to develop an intergenerational movement program for grandchildren and grandparents to improve co-PA, physical activity, cognitive functioning, psychosocial well-being and the quality of the relationship in grandchildren and grandparents. First of all, many children and older adults do not meet the physical activity guidelines of the WHO. Secondly, this program will be developed using a co-creation approach together with a theoretical framework “Behaviour Change Wheel”, because it is really important to take needs and requirements of the target group into account and to develop an intervention in an evidence-based way. Thirdly, intergenerational programs are scarce in relatives and the quality of the family relationship between grandchildren and grandparents has not yet been investigated while doing organized activities together. Lastly, the combination of physical activity and cognitively enriched activities has never been used in intergenerational research. Therefore, developing a cognitively enriched, intergenerational movement program for grandchildren and their grandparents is innovative.	pp. 19–20	_____________
	**WHAT**		
3.	Materials: All the variables (physical activity, cognitive functioning, psychosocial well-being and quality of the family relationship) will be measured pre (at baseline, before the start of the sessions), post (after 24 weeks, right after the RCT ends), and for the third period at follow-up (after 36 weeks). To objectively measure physical activity, grandchildren and grandparents will have to wear Axivity AX3 accelerometers (wrist of the non-dominant hand) or ActiGraph wGT3X-BT (right hip). Grandparents and grandchildren also have to wear these accelerometers during certain sessions to measure the intensity of the activities that they do together. A seven-day diary will be used to study the context of co-PA. Cognitive functioning will be objectively quantified with the validated neuropsychological test battery (i.e., CANTAB) (cambridgecognition.com) using an iPad 10.2. Psychosocial well-being will be measured by several questionnaires that administer well-being indicators relevant for children and older adults. For children: PEDs-QL (Pediatric health-related Quality of Life scale). For older adults: Warwick-Edinburgh Mental Well-Being Scale (WEMWBS), Four-Dimensional Symptom Questionnaire (4DSQ), Social and Emotional Loneliness scale for Adults (SELSA). Quality of the family relationship will be measured in children with the Grandparent-grandchild Relationship Questionnaire. For older adults, this will be measured with a self-report questionnaire, based on previous investigations of Farneti & Battistelli.	pp. 16–17	_____________
4.	Procedure: Convenience sampling will be used to recruit participants for the RCT. A first strategy will be to reach out to children via schools in the city of Ghent and contact their grandparents (via their parents). All children of the first and the second grade (class 1 till 4 of the primary school) of 2 schools will receive an information letter about the goal of the study and some explanation about the RCT. In case of too low respondents, additional schools or GRAY will be addressed. If both children and their grandparents are interested to participate (parents must ask the grandparents), they can fill in their contact information using a paper strip attached to the information letter. Of those that responded to be interested to join, the researcher will call the parents and grandparents to ask some questions to administer sociodemographic characteristics (i.e., age, gender) and inclusion criteria (i.e., language, physical, cognitive and psychological health status) of grandchildren and grandparents. Before participation in the RCT, participants will be asked to sign an informed consent. Grandchildren will need parental consent and will also be asked for an informed assent themselves; grandparents will sign an informed consent for themselves.	p. 10	_____________
	**WHO PROVIDED**		
5.	The co-creation sessions will be led by researchers and facilitators (background in movement and sports sciences, psychology and health promotion) who will have received a training in co-creation. This information is given, because the co-creation sessions are an important element for the development of the movement program and for the intervention itself. The intergenerational movement sessions will be worked out by experts in movement and sports sciences together with organizations who work with children and older adults (MOEV, Family Sports Flanders, GRAY). The intergenerational movement sessions itself will be led by students and experts in movement and sports sciences.	pp. 9, 13	_____________
	**HOW**		
6.	The intergenerational movement sessions will be provided in a group. Approximately 20 to 30 grandchildren and grandparents per group will be able to participate in the sessions (but group size also depends on preferences of the participants) and 1 or 2 experts in movement and sports sciences will lead these sessions.	p. 13	_____________

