#### 2.2.3. Randomized Controlled Trial (RCT)

The RCT will be conducted subsequent to the pilot study so as to measure the effects of the two different programs on the outcomes of PA, cognitive functioning, psychosocial well-being, and quality of the family relationship in the grandchildren and grandparents and to evaluate the process of the study. The RCT will consist of two intervention groups, Arm 1: Intergenerational PA and Arm 2: Cognitively enriched intergenerational PA, and one control group. Intervention Group 1 will receive the intergenerational movement program, Intervention Group 2 will receive the cognitively enriched intergenerational movement program, and the control group will receive no intervention. The pre- (before the start of the sessions), post- (after 24 weeks) and follow-up (after 36 weeks) outcome measures of PA, cognitive functioning, psychosocial well-being, and quality of the family relationship will be compared between Group 1 and the control group, between Group 2 and the control group, and between Groups 1 and 2. An overview of the RCT is shown in Figure 5.

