##### Participants and Sample Size

The same inclusion criteria will be used for the RCT as in the co-creation trajectories and the pilot study (i.e., speaking Dutch; having at least one grandparent or grandchild; and having no serious physical, cognitive, or psychological health problems). Based on effect sizes of intergenerational programs of children and older adults, an effect size of 0.15 will be intended for the outcomes of PA, cognitive functioning, psychosocial well-being, and quality of the family relationship [65]. The required sample size has been calculated using the software GPower 3.1.9.7 (Universität Düsseldorf, Düsseldorf, Germany) [60]. The sample calculation will be based on 80% power to detect a significant difference in PA, cognitive functioning, psychosocial well-being, and quality of the family relationship between groups and over time. Significance level alpha 0.05, having 3 groups (2 intervention groups and 1 control group) and 3 measurements (pre-, post-, and follow-up). A priori power analysis for the RCT suggests a total sample size of around 45 dyads (*n* = 90 grandchildren and grandparents). Assuming an attrition rate of 20% [61], a total sample size of 54 dyads (*n* = 108 grandchildren and grandparents) will be required for the 3 groups. (Each group consists of 36 participants: 18 grandchildren and 18 grandparents). See Figure 4.

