##### Data Analysis

Multilevel linear analysis in R will be used to estimate the between and within subject effects on PA, cognitive functioning, psychosocial well-being, and the quality of the familial relationship in grandchildren and grandparents. The mediating role of co-PA in the relationship between PA, cognitive functioning, psychosocial well-being, and the quality of the family relationship will be statistically checked in R using structural equation modelling (path analysis). Open-ended questions will be conducted using content analysis in SPSS (i.e., creating a code tree and looking for themes in the responses) [64].

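### The stated 80% power makes no allowance for clustering by session group in the two active arms, and the number of session groups per arm is not fixed

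*Protocol article*

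**What the plan says.** Appendix A (TIDieR checklist, item 6) describes delivery: "The intergenerational movement sessions will be provided in a group". It gives the size, "Approximately 20 to 30 grandchildren and grandparents per group will be able to participate in the sessions", adds that this also depends on participants' preferences, and says that "1 or 2 experts in movement and sports sciences will lead these sessions". Section 2.2.3 sets two active arms against a third arm: "the control group will receive no intervention". The sessions number 12 or 24 over 24 weeks.

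Under Participants and Sample Size for the RCT, "an effect size of 0.15 will be intended for the outcomes of PA, cognitive functioning, psychosocial well-being" and the quality of the family relationship. On power: "The sample calculation will be based on 80% power to detect a significant difference in PA, cognitive functioning" and the other outcomes, between groups and over time. The remaining GPower inputs are alpha 0.05, 3 groups and 3 measurements. The result is about 45 dyads (90 people), raised to 54 dyads (108 people) for attrition, so that "Each group consists of 36 participants: 18 grandchildren and 18 grandparents". No intraclass correlation or design effect appears.

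The RCT Data Analysis paragraph plans a multilevel linear analysis in R "to estimate the between and within subject effects" on the outcomes. It does not list the levels of the model and mentions neither session group nor dyad.

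**The concern.** People who attend the same sessions for half a year share peers, a time slot and whoever leads the session. If that makes their outcomes more alike, 30 people in one session group carry less information than 30 unconnected people. The design is partially nested: clustering can arise in Arms 1 and 2 but not among controls.

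Two things are at stake. First, the stated power holds only if the session-group ICC is zero. Second, the number of session groups per arm decides what the trial can conclude. Arm 2 against Arm 1 tests whether cognitive enrichment adds to cognitive functioning, and both sides of that contrast are clustered. If each arm is a single session group, a difference between the arms cannot be told apart from a difference between two particular groups, and no later model can repair that.

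**Working it through.** **Inputs from the article:** effect size 0.15, 80% power, alpha 0.05, k = 3 groups, m = 3 measurements, 90 people before attrition, 36 enrolled per arm, session groups of about 20 to 30.

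**Assumptions, because the article gives no figure:** 0.15 is Cohen's f; correlation between repeated measures ρ = 0.5; sphericity; session-group ICC of 0.02, 0.05 or 0.10.

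**Step 1. Reproduce the stated size.** For the groups-by-time interaction in a repeated-measures ANOVA:

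- λ = f²·N·m/(1 − ρ) = 0.0225 × 90 × 3/0.5 = 12.15
- df1 = (3 − 1)(3 − 1) = 4; df2 = (90 − 3)(3 − 1) = 174
- Power = 79.6% at N = 90. The smallest N reaching 80% is 91.

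The stated 90 is therefore what the standard formula gives for 90 independent individuals. If the 45 is instead read as a count of dyads, the formula needs ρ of about 0.75 (N = 47 at exactly 0.75). That reading has no session-group allowance either.

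**Step 2. Add clustering in two of three arms.** With n people per session group, DE = 1 + (n − 1) × ICC. Averaged over two clustered arms and one unclustered arm, DE* = (2·DE + 1)/3. The noncentrality becomes λ/DE*. This is an approximation.

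| Group size | ICC | DE | DE* | λ/DE* | Power at N = 90 |
|---|---|---|---|---|---|
| 20 | 0.02 | 1.38 | 1.25 | 9.69 | 69% |
| 20 | 0.05 | 1.95 | 1.63 | 7.44 | 56% |
| 20 | 0.10 | 2.90 | 2.27 | 5.36 | 41% |
| 30 | 0.02 | 1.58 | 1.39 | 8.76 | 64% |
| 30 | 0.05 | 2.45 | 1.97 | 6.18 | 47% |
| 30 | 0.10 | 3.90 | 2.93 | 4.14 | 32% |

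At ICC 0.01, power is 74% (groups of 20) or 71% (groups of 30). If the 30 people per arm were split into two groups of 15, power would be 71%, 61% and 48% at ICC 0.02, 0.05 and 0.10.

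**Step 3. Number of session groups per arm.** At enrolment, 36/30 = 1.2 and 36/20 = 1.8, so an arm is either one group above the stated size or two groups at or below its lower end (18 each). At the 45 dyads required before attrition, each arm has 15 dyads, or 30 people, which fits one group. Both layouts are open.

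**Step 4. Standard errors if session group is left out of the model.** The true standard error exceeds the naive one by √DE for Arm 2 against Arm 1, and by √((DE + 1)/2) for an active arm against control. At ICC 0.02, 0.05 and 0.10:

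- Groups of 20: 1.17, 1.40, 1.70 between active arms; 1.09, 1.21, 1.40 against control.
- Groups of 30: 1.26, 1.57, 1.97 between active arms; 1.14, 1.31, 1.57 against control.

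A simulation illustrates the effect on a nominal 5% test: 40,000 trials, 18 dyads per arm, one generation, one time point, and a two-sample t-test that ignores session group. Rejection rates under no effect were:

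| Contrast | Session groups per arm | ICC 0.02 | ICC 0.05 | ICC 0.10 |
|---|---|---|---|---|
| Active v control | 2 | 6% | 8% | 10% |
| Active v control | 1 | 7% | 10% | 15% |
| Arm 2 v Arm 1 | 2 | 7% | 10% | 15% |
| Arm 2 v Arm 1 | 1 | 9% | 15% | 25% |

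**The case against.** The strongest objection concerns the analysis. A reader might infer that the planned analysis treats participants as independent, so that standard errors are bound to be too small. The article does not say that. It names a multilevel model, a method for correlated data, and describes between- and within-subject effects as what is estimated, not as the full list of levels. The random-effects structure may be set out in an analysis plan that is not shown. This objection stands: the results in Step 4 are conditional on session group being omitted and the ICC being above zero, and the simulated t-test is simpler than the planned model.

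A reader might also infer that the session leader is confounded with arm. The article does not show this. Checklist items 5 and 6 say that students and experts lead the sessions, one or two experts at a time, without assigning anyone to an arm. The same staff could lead both.

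Nor does the article establish that each arm must run as two groups. The group size is approximate and depends on preferences, 30 people per arm would fit one group, and the 12 dyads per group in the pilot was a pilot choice. Random allocation to session groups would also conflict with holding sessions at times that families prefer.

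Finally, nothing in the article supports a particular ICC. Accelerometry, cognitive tests and questionnaires are measured on individuals, and the correlation may be small. That is fair, and it is why only a range is given. None of this touches the power statement, which the article has fixed with its inputs listed.

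**Conclusion.** The point holds for the power statement and for the unstated number of session groups. The 80% is right only if the session-group ICC is zero. Over assumed ICCs of 0.02 to 0.10, power at 90 people is about 69% to 41% with groups of 20 and 64% to 32% with groups of 30. These figures rest on reading 0.15 as Cohen's f, on ρ = 0.5, and on an averaged design effect.

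For the analysis, the conclusion is conditional: standard errors will be too small if session group is omitted and the ICC is above zero, with the largest shortfall for Arm 2 against Arm 1. With one session group per arm, the group effect cannot be separated from the arm effect, whatever model is fitted.

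**What to change.** - In Participants and Sample Size, restate the power over a stated ICC range with a partially nested design effect. No larger enrolment is asked for. For scale, multiplying 90 by DE* gives about 113, 147 and 204 people for groups of 20 at ICC 0.02, 0.05 and 0.10.
- Reconcile 36 people per arm with 20 to 30 per session group by stating how many session groups each active arm will have.
- Where an arm has more than one session group, include session group as a level in the active arms only, with controls as singletons, and use small-sample degrees of freedom.
- One or two groups per arm cannot estimate that variance well. Report the arm contrasts with standard errors inflated over the same ICC range as a sensitivity analysis, and state the resulting limit on the Arm 2 against Arm 1 conclusion.

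The cost is a less favourable stated power and wider sensitivity intervals. The changes are to wording and analysis; they do not require random allocation to session groups or a minimum of two groups per arm.

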	**WHERE**		
7.	The intervention will take place in Ghent, where the researchers are situated. Depending on the preferences of grandchildren and grandparents, the sessions will take place indoor or outdoor. It will also depend on the topics and needed materials whether some sessions will take place outside or not.	p. 13	_____________
	**WHEN and HOW MUCH**		
8.	Grandchildren and their grandparents will participate in a cognitively enriched movement program, which will be developed by themselves together with the researchers (co-creation). The preferences and needs of the target group will determine what the program will look like. A total of 12 (or 24) sessions (one/two session(s) every (two) week(s) per group will take place during 24 weeks on a preferred time during the week (e.g., Wednesday afternoon, Tuesday evening, Thursday evening…). There will be two arms, arm 1 will receive only movement activities, arm 2 will receive cognitively enriched movement activities. The content of the sessions (duration, topics, format, materials) will be refined after the pilot study. Intervention groups will receive a brochure with (cognitively enriched) movement activities they can perform at home after the follow-up measurement to create a long-term effect. This part of the checklist will be refined after the pilot study, when there is more information available about the movement sessions.	p. 16	_____________
	**TAILORING**		
9.	If the intervention was planned to be personalised, titrated or adapted, then describe what, why, when, and how. Not applicable for this intervention.		_____________
	**MODIFICATIONS**		
10. ^ǂ^	If the intervention was modified during the course of the study, describe the changes (what, why, when, and how). This will be described when the RCT has ended.		_____________
	**HOW WELL**		
11.	To assess intervention adherence and fidelity, a protocol study has been written out to think about different aspects (participants, sample size, measurement instruments) in order to reduce bias. Furthermore, providers of the intervention will have received a training or will be experts in what they have to perform. The measurement instruments that will be used during the intervention are all validated and reliable for children and older adults.	pp. 13, 16–17	_____________
12. ^ǂ^	Actual: If intervention adherence or fidelity was assessed, describe the extent to which the intervention was delivered as planned. This will be described when the RCT has ended.		_____________

** **Authors**—use N/A if an item is not applicable for the intervention being described. **Reviewers**—use ‘?’ if information about the element is not reported/not sufficiently reported. † If the information is not provided in the primary paper, give details of where this information is available. This may include locations such as a published protocol or other published papers (provide citation details) or a website (provide the URL). ǂ If completing the TIDieR checklist for a protocol, these items are not relevant to the protocol and cannot be described until the study is complete. Note 1: We strongly recommend using this checklist in conjunction with the TIDieR guide (see *BMJ* 2014; 348: g1687) which contains an explanation and elaboration for each item. Note 2: The focus of TIDieR is on reporting details of the intervention elements (and where relevant, comparison elements) of a study. Other elements and methodological features of studies are covered by other reporting statements and checklists and have not been duplicated as part of the TIDieR checklist. When a **randomised trial** is being reported, the TIDieR checklist should be used in conjunction with the CONSORT statement (see www.consort-statement.org) as an extension of **Item 5 of the CONSORT 2010 Statement.** When a **clinical trial protocol** is being reported, the TIDieR checklist should be used in conjunction with the SPIRIT statement as an extension of **Item 11 of the SPIRIT 2013 Statement** (see www.spirit-statement.org). For alternate study designs, TIDieR can be used in conjunction with the appropriate checklist for that study design (see www.equator-network.org).
